### Development of the AI Algorithm

We will develop an individual AI algorithm for automatic interpretation of radiologic signs of cardiac decompensation on chest CT scans, but the algorithm will also serve as a foundation for pneumonia and pulmonary embolism. The model will be trained to detect each condition, pulmonary congestion, pneumonia, and pulmonary embolism, independently, using a multilabel approach with separate binary classifiers. This allows more than one condition to be identified in the same scan. The CT scans were extracted in pseudonymized form.

Participants will be randomly split on the participant level into training (2/3) and internal test data (1/3; Figure 1). This process will be carried out separately for each of the 3 diseases, creating distinct AI models for each. We will train boosted tree prediction models using volume, diameter, and density measurements from structures segmented in the CT images. The segmentations will be derived from TotalSegmentator, extreme gradient boosting, and in-house codes [16,17].

We do not expect substantial missing data, as all CT scans will be extracted retrospectively without patient consent. Extreme, noisy, or missing feature values, typically caused by segmentation errors, will be handled by allowing them as many splits as possible in the tree-based model. To develop the model, a three-step procedure will be applied for boosted trees models: (1) parameter tuning with all features, (2) feature selection by forward selection guided by internal feature importance measures of extreme gradient boosting, and (3) retuning with the selected features. Hyperparameter optimization will be conducted by grid search using the area under the receiver operating characteristic curve as the evaluation metric. Parameter tuning and feature selection will be performed on the training data with stratified 3-fold cross validation, defined at the participant level and kept consistent across all steps.

We will use grid search and forward feature selection to find the best parameters. To further assess performance and enhance model interpretability, results will be presented using Shapley Additive Explanations (SHAP) [18]. The overall impact of each feature will be illustrated with SHAP beeswarm and bar plots. SHAP waterfall plots will explain the contribution of individual features to specific predictions, supported by visual inspection of the corresponding segmentations. This analysis allows for the removal of features deemed clinically unimportant or redundant. To evaluate the AI algorithms, they will be qualitatively evaluated by visual inspection, including segmentations. We will qualitatively evaluate the AI algorithms and model predictions using receiver operating curve (ROC) curves and confusion matrices of the thresholded predictions. False positives and false negatives will be evaluated by chief physicians with a special interest in thorax radiology.

### Ground Truth for Development and Validation of the AI Algorithm

The ground truth for the development and validation will be the radiological description of each CT scan, prepared by the on-call radiologist following standard clinical procedures. The on-call radiologists include both board-certified specialists and junior radiologists in training. All final assessments are supervised by a board-certified radiologist. All radiological reports are produced as part of routine clinical practice, and while variations in descriptions may occur due to specific clinical focuses of the scans, the regional standard reporting procedures ensure a consistent approach to assessing pathologies. These radiological findings will be extracted from the radiology reports (PDF) using a set of regular expressions for the selected diseases. The report clinical labels for cardiac decompensation may encompass terms such as pulmonary congestion, pulmonary edema, heart failure, and decompensation in the description of the radiologist. A subset of training data will be used to iteratively improve expressions. All reports containing these indicators, whether affirming or negating their presence, will be manually reviewed to correct any labeling errors. All labels will be reviewed for technical accuracy, with unclear cases assessed by project clinicians. False positives and negatives will be evaluated by chief physicians specializing in thoracic radiology.

Given the large volume of scans, manual review by an expert radiologist is impractical and resource intensive, but this approach maximizes the dataset, reflects real-world workflow, and mitigates risks to model validity.

### Target Condition Distribution

Previous studies from Denmark have reported that acute heart failure accounts for approximately 6% of medical hospital admissions among adults [19], that the incidence of pneumonia requiring hospitalization was 442 per 100,000 person years in 2003 [20], and that the incidence of pulmonary embolism requiring hospitalization occurs at a rate of 64 per 100,000 adults annually [21]. Preliminary labeling of the development dataset shows a similar distribution, with 7% to 8% positive for cardiac decompensation, while labeling for pneumonia and pulmonary embolism is still ongoing.

### Validation of the AI Algorithm

The AI algorithms will be internally validated using the area under the curve from ROC curves and confusion matrices. Optimal thresholds for the likelihood of heart and lung diseases will be obtained from the validation cohort and defined by a true positive rate and true negative rate of 90% or greater. These thresholds will be tested for the prediction of heart and lung diseases in the validation cohorts.

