**Methods:**

We designed a retrospective method development and validation study. This study has been approved by the Danish National Committee on Health Research Ethics (1575037). We extracted 4672 acute chest CT scans with corresponding radiological reports from the Copenhagen University Hospital–Bispebjerg and Frederiksberg, Denmark, from 2016 to 2021. The scans will be randomly split into training (2/3) and internal validation (1/3) sets. Development of the AI algorithm involves parameter tuning and feature selection using cross validation. Internal validation uses radiological reports as the ground truth, with algorithm-specific thresholds based on true positive and negative rates of 90% or greater for heart and lung diseases. The AI models will be validated in low-dose chest CT scans from consecutive patients admitted with acute dyspnea and in coronary CT angiography scans from patients with acute coronary syndrome.

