### Statistical Analyses

In each validation cohort, the default thresholds obtained from the internal validation will be used to calculate the diagnostic ability of the AI algorithm to predict the prespecified heart and lung diseases. We will, for all diagnoses, calculate odds ratios, sensitivity, specificity, positive and negative predictive values, positive and negative likelihood ratios, and area under the curve from the ROC curves.

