#### Mitigating Imaging Variability and Validation Thresholds

Differences in imaging protocols across cohorts, including variations in scanner type, reconstruction kernels, and acquisition parameters, may affect AI model performance. To address this, the algorithm will be developed using data from multiple manufacturers, image types, and reconstruction kernels, and it will include both contrast-enhanced and noncontrast scans. This approach is designed to minimize the impact of technical variability and improve generalizability across different clinical settings, reducing the risk of bias from scanner settings and acquisition protocols. Planned cross-cohort validation will further ensure the robustness of the algorithm.

The sensitivity and specificity thresholds of 90% or greater chosen for validation are ambitious, but they align with performance levels generally regarded as necessary for clinical decision support in acute care, where the consequences of false negatives and false positives can be substantial. Thus, these thresholds serve as a target for ensuring patient safety and diagnostic reliability. We acknowledge that achieving such levels may involve trade-offs, including impaired sensitivity-specificity balance or reduced generalizability due to increased model complexity. High false positive rates could burden clinicians with unnecessary alerts, while false negatives might delay diagnosis of critical conditions.

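### The default threshold is chosen and reported on the same internal third, and the 90%/90% rule does not define a single cut-off

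*Protocol article*

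**What the plan says.** All references are to the protocol article.

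- **Split.** Development of the AI Algorithm divides participants into a training part (2/3) and an internal test part (1/3). Tuning and feature selection stay in the training part under 3-fold cross-validation. The threshold is not listed among those steps, and no third part is set aside for it.
- **Source of the threshold.** Validation of the AI Algorithm states: "Optimal thresholds for the likelihood of heart and lung diseases will be obtained from the validation cohort and defined by a true positive rate"; sensitivity and specificity must both reach 90%. Statistical Analyses identifies the cohort: "the default thresholds obtained from the internal validation will be used to calculate the diagnostic ability of the AI algorithm".
- **Internal reporting.** The same validation section assesses the algorithms internally by AUC and confusion matrices. The development section says that the confusion matrices are those of thresholded predictions. The abstract also ties the cut-offs to internal validation: "with algorithm-specific thresholds based on true positive and negative rates of 90% or greater for heart and lung diseases".
- **Later use.** "These thresholds will be tested for the prediction of heart and lung diseases in the validation cohorts".
- **Status of the 90% levels.** The Discussion says: "The sensitivity and specificity thresholds of 90% or greater chosen for validation are ambitious". It then calls them a target and accepts that reaching them may involve trade-offs.

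**The concern.** There are two separate difficulties.

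First, the held-out third does two jobs. It supplies the cut-off and then the confusion matrix at that cut-off. A cut-off tuned to the sample in which it is assessed looks better there than it will elsewhere, so the internal third no longer gives a clean estimate of sensitivity or of the figures derived from it (predictive values, likelihood ratios, odds ratio). This matters most for pulmonary embolism, for which the article names no external cohort, so its internal figures stand alone.

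Second, two inequalities are a performance requirement, not a selection rule. They may be satisfied by no cut-off or by many, and the article gives neither a fallback nor a tie-break. Yet the default threshold is needed for every diagnostic measure in each validation cohort, and for the AI-generated label of decompensation whose prognostic value is to be studied in VERDICT and CATCH.

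**Working it through.** The article states no expected AUC and no calculation for this point, so there is no figure of its own to reproduce.

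**Inputs from the article:** 4672 patients (Training and Internal Validation Cohort); one third held out (Development of the AI Algorithm); 7% to 8% positive for cardiac decompensation (Target Condition Distribution); both rates at least 90% (Validation of the AI Algorithm).

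**Assumptions:** scores are normal with equal variance in positives and negatives; a range of true AUCs is shown. Sizes are for cardiac decompensation only, because labelling of the other two conditions is unfinished.

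**Step 1, size of the internal third.** 4672/3 ≈ 1557 patients. At 7.5% this is about 117 positives and 1440 negatives (109 to 125 positives over the 7% to 8% range).

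**Step 2, AUC needed for a 90/90 point.** Separation d = 2 × z(0.90) = 2 × 1.2816 = 2.563. AUC = Φ(2.563/√2) = 0.965.
- At AUC 0.95, d = √2 × z(0.95) = 2.326. The best balanced point is Φ(2.326/2) = 87.8% for both rates, and specificity at 90% sensitivity is Φ(2.326 − 1.2816) = 85.2%.
- At AUC 0.98, d = √2 × z(0.98) = 2.904. Any cut-off with sensitivity between 90.0% and Φ(2.904 − 1.2816) = 94.8% qualifies.

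**Step 3, does the rule give a cut-off?** Simulation with 4000 datasets per AUC, 117 positives and 1440 negatives. The last column applies when a qualifying cut-off was found and the one with the largest sum of sensitivity and specificity was taken.

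| True AUC | Datasets with a qualifying cut-off | Median number of qualifying cut-offs | Sensitivity overstated by (points) |
|---|---|---|---|
| 0.90 | 0% | – | – |
| 0.95 | 7% | 13 | 6.5 |
| 0.96 | 30% | 21 | 4.4 |
| 0.965 | 50% | 29 | 3.4 |
| 0.97 | 74% | 39 | 2.5 |
| 0.98 | 98% | 76 | 1.7 |
| 0.99 | 100% | 121 | 1.6 |

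The qualifying cut-offs span about 5 points of true sensitivity at AUC 0.98 and about 8 points at 0.99.

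**Step 4, optimism from choosing and judging on the same third, averaged over all datasets.**
- Cut-off maximising the smaller rate, model truly at 90/90: about 0.9 points in sensitivity and 0.02 to 0.03 points in specificity. A re-run gave 0.5 to 0.9 points in sensitivity, depending on which of several tied cut-offs is taken.
- Cut-off maximising the sum of the rates: 1.6 to 2.9 points in sensitivity and 0.1 to 0.2 points in specificity over AUC 0.85 to 0.99.
- If a qualifying cut-off has been found and the smaller rate is maximised, the re-run gave 1.7 points at AUC 0.97, 3.8 at 0.96 and 6.1 at 0.95. These are close to the table.

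**Step 5, precision for comparison.** A sensitivity of 105/117 = 89.7% has an exact 95% interval of 82.8% to 94.6%. A specificity of 1296/1440 = 90.0% has 88.3% to 91.5%.

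**The case against.** **Independent testing is planned.** The thresholds are carried forward, FACTUAL patients were kept out of development, and every FACTUAL scan was read by two blinded thoracic radiologists. Choosing a cut-off on held-out data and testing it elsewhere is a recognised design. This stands for FACTUAL: a reader might infer that the external accuracy is inflated as well, but a frozen cut-off applied to new patients is not made optimistic by how it was chosen. It does not rescue the internal figures. FACTUAL has 242 patients and covers decompensation and pneumonia only, and the article says that VERDICT and CATCH lack radiological reports.

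**The bias is small.** Largely true. The average optimism lies well inside the sampling interval in Step 5, specificity hardly moves, and internal AUC does not depend on the threshold. The bias becomes material only when a qualifying cut-off is found for a model near or below the 90/90 boundary.

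**The plural may mean two operating points**, one at 90% sensitivity and one at 90% specificity, each of which always exists. The wording allows this. But then the article does not say which one is the default, and both are still chosen on the internal third.

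**Tie-break and fallback can wait for an analysis plan or the promised methods article.** Partly true. The data source and the two-sided rule, however, are already fixed in the text, and those are the defects.

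Two stronger readings are not supported. A reader might infer that models will too often be declared to have passed 90/90, but the article sets no declaration rule and calls the levels a target. A reader might also infer from "This analysis allows for the removal of features deemed clinically unimportant or redundant" that features are dropped after looking at test data. That sentence stands in the development section, which keeps feature selection in the training data.

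**Conclusion.** The point holds in limited form. As written, the internal third both sets and assesses the cut-off, so internal threshold-based figures are optimistic, almost entirely through sensitivity: up to about 1 point on average if the smaller rate is maximised, and about 2 to 6 points when a qualifying cut-off is found at a true AUC of 0.97 down to 0.95.

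The more serious defect is that the rule does not fix a cut-off. As one cut-off per disease, it most often yields nothing at a true AUC of 0.96 or below, is an even chance at 0.965, and leaves dozens of candidates at 0.98. As two cut-offs, it leaves the default unnamed. Every later threshold-based analysis depends on it.

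The sizes rest on the equal-variance binormal assumption and a 7.5% prevalence. That the rule is incomplete, and that the same third is used twice, follows from the text alone.

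**What to change.** In Validation of the AI Algorithm and Statistical Analyses:

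1. Choose one threshold per disease from the out-of-fold predictions of the existing cross-validation in the training data, by a rule that always gives an answer. One example is the cut-off maximising the smaller of sensitivity and specificity, with a stated tie-break.
2. Lock model and threshold before the internal third is opened, and apply both unchanged there and in the validation cohorts.
3. State 90%/90% as a performance target, as the Discussion already does, and report the internal sensitivity and specificity against it with 95% confidence intervals.

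The cost is a change of wording and one further output from the cross-validation. There are two drawbacks. Internal figures become slightly less favourable. And because the same folds serve tuning and feature selection, and the fold models are fitted to fewer data, the cut-off may sit slightly off the optimum for the refitted model. That can cost a little performance but does not bias the estimates from the internal third.

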### Validation in Chest CT Scans in the Clinical FACTUAL Cohort

The AI algorithm for not only cardiac decompensation but also pneumonia will be validated in a previously performed clinical prospective observational study. The study included 242 consecutive patients with dyspnea, who underwent acute low-dose, noncontrast, chest CT scans within 12 hours from admission (FACTUAL study [H-17000869]; Textbox 1) [7]. CT scans were acquired without contrast at low dose (<2 mSv) using a multislice scanner and standard lung and soft tissue reconstruction kernels. A firewall ensured that none of these patients were included in the AI development sets.

Inclusion and exclusion criteria for the FACTUAL, VERDICT (Very Early Versus Deferred Invasive Evaluation Using Computerized Tomography), and CATCH (Cardiac CT in the Treatment of Acute Chest Pain) studies.
**Inclusion criteria for the FACTUAL study**
Aged >50 yearsAcute dyspnea, combined with at least 1 abnormal objective parameter supporting respiratory imbalanceRespiratory rate of more than 20 breaths per minuteSaturation below 95% (if known chronic obstructive pulmonary disease (COPD) below 92%)Abnormal partial pressure of oxygen (pO2) or partial pressure of carbon dioxide (pCO2) in arterial bloodObjective signs of heart failure (ie, jugular vein distention, peripheral edema, orthopnea, and bilateral rales on auscultation)Rhonchi or prolonged breathing on auscultation
**Exclusion criteria for the FACTUAL study (none of the exclusion criteria must be met)**
All study examinations, including low-dose chest computed tomography (CT) scans, performed later than 12 hours after admissionPatients who are unstableRequiring ventilation (including noninvasive ventilation)Requiring intensive care (inotropic treatment)Requiring telemetry due to acute coronary syndromePatients who refuse or cannot provide consent (ie, mental illness [eg, dementia] and language barriers)Patients without Danish citizenshipLife expectancy <3 months (assessed by the emergency department physician)CT thorax already indicated (pulmonary embolism, aortic dissection, or aneurysm)Patients who are isolated (ie, vancomycin-resistant *Escherichia coli* and influenza)
**Inclusion criteria for the VERDICT study**
Invasive coronary angiography clinically indicated and logistically possible within 12 hours from the non–ST-segment elevation acute coronary syndrome (NSTE-ACS) diagnosisAged >18 yearsClinical suspicion of ACS, combined with at least one of the following high-risk criteria:Electrocardiogram (ECG) changes indicating new ischemia (new ST-segment depression, horizontal or downsloping ≥0.05 mV in 2 consecutive leads, and T-wave inversion >0.01 mV in 2 leads with prominent R-wave or R/S ratio >1)An increase in coronary markers of ischemia (troponin)
**Exclusion criteria for the VERDICT study (none of the exclusion criteria must be met)**
PregnancyPatients who refused or could not provide consentIndication for acute invasive coronary angiography (very high-risk NSTE-ACS)Life expectancy <1 yearKnown intolerance to platelet inhibitors, heparin, or x-ray contrast that could not be remedied medicallyPrevious coronary artery bypass graftingCreatinine >140 μmol/LKnown atrial fibrillationWomen aged <45 years were not considered eligible for coronary CT angiography
**Inclusion criteria for the CATCH study**
Hospitalized with suspicion of NSTE-ACSNormal or nondiagnostic ECG findingsNormal troponinsDischarged within 24 hours without recurrence of chest painClinical indication for further noninvasive, outpatient cardiac evaluation, evaluated by the treating physician
**Exclusion criteria for the CATCH study (none of the exclusion criteria must be met)**
Aged <18 yearsNew diagnostic ECG changes with ST-segment elevation or depression >0.5 mm or T-wave inversion >4 mm in ≥2 contiguous leadsWomen of childbearing age not using approved contraceptionGeographical residence or mental or physical conditions that could complicate follow-upKnown allergy to iodinated contrast agentsSerum creatinine >130 mg/LAbnormal chest radiography or blood test results that could explain chest painPrevious coronary artery bypass graftingPatients who refused or could not provide consent

The primary outcome is to validate the diagnosis of the AI algorithm in identifying the following: (1) normal CT images without treatment-requiring pulmonary changes, (2) radiological signs of cardiac decompensation, and (3) radiological infiltrates indicative of pneumonia.

The gold standard is the radiological evaluation of the CT images, which were analyzed in 2 ways:

Randomly analyzed by the on-call clinical radiologists according to clinical standards. The on-call radiologists had access to the medical journal, laboratory reports, and previous radiology images. The workflow is as follows: a radiology report is made by the on-call clinical radiologist and subsequently approved by a senior radiologist.Two blinded, independent specialist thoracic radiologists evaluated every CT scan for distinct signs of heart and pulmonary diseases according to the Fleischner Society list [7,22].

### Validation in Coronary CT Angiograms in the VERDICT and the CATCH Studies

#### Overview

We aim to calibrate and validate the AI algorithm for cardiac decompensation on coronary CT angiographies (CCTA) in the Very Early Versus Deferred Invasive Evaluation Using Computerized Tomography (VERDICT) trial and in the Cardiac CT in the Treatment of Acute Chest Pain (CATCH) trial.

#### VERDICT Study

The VERDICT study was a large-scale randomized-controlled trial conducted in the Capital Region, Denmark, that included 2147 patients with non–ST-segment elevation acute coronary syndrome (NSTE-ACS). Patients were randomized to invasive coronary angiography within 12 hours or standard invasive care within 48 to 72 hours. In a substudy, 1023 participants from both groups underwent CCTA before the invasive procedure (Textbox 1) [23]. CCTA was performed on 64- or 320-detector scanners, predominantly with prospective electrocardiogram-triggering and intravenous contrast injection [23].

